#### Sample size estimation

Sample size calculation was performed based on *BMAL1* gene expression data from our previous work [34] assuming that all measurements follow a sinusoidal wave function $y_{i}=A\;sin\;(\omega (t_{i}+\phi ))+M+\varepsilon_{i}$, 1 ≤ i ≤ n whereby n is the total number of samples, $\omega =\frac{2\pi }{Period}$ the frequency of the sinusoidal wave, φ the phase shift, M the rhythm-adjusted mean (MESOR), and t_i_ the observed Zeitgeber time. ε_i_ is the error term for sample i. We assume ε_i_ are identically and independently distributed from $\varepsilon_{i}∼N(0,\sigma^{2})$, where σ is the noise level. The null hypothesis that there is no circadian rhythmicity (H_0_ = 0) is tested against the alternative hypothesis that a circadian rhythmicity pattern exists (H_A_≠0). Rhythmicity will be tested using the F-test which compares the fitted model against a restricted model. For details see please Cornelissen [39]. The study is considered successful if rhythmicity is detected in the measured core-clock and clock-controlled genes obtained from saliva samples. To account for multiple comparisons (comparisons between gender and age subgroups and various seasons, in total up to 10 comparisons) the type I error is set to 0.005 according to the Bonferroni correction to hold the global significance level of α = 0.05. Underlying the data of our previous study [34], an amplitude (A) of 1.11 is estimated for *BMAL1* gene expression and the standard deviation of residuals (s) is 1.36, which gives an estimate of the intrinsic effect height of r = A/s = 0.82.

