### Outcome measures

#### Primary outcome measure

Circadian profiles of gene expression from saliva samples of healthy, physically active individuals to characterize the CR. The participants will be provided four saliva sampling home kits with which they can collect their data during the four different rounds (each round of sampling collection carried out over two consecutive days) within the suggested season (spring/summer or autumn/winter) batch, see section ‘*Study Design’* for further details. Time series analysis of 8 core-clock and clock-controlled genes, *BMAL1*, *PER2*, *CRY2*, *NR1D2*, *AKT1*, *SIRT1*, *IL6*, *PDHB*, *GAPDH* (Glyceraldehyde-3-Phosphate Dehydrogenase housekeeping gene/internal reference gene), will be measured to quantify CR characteristics with respect to phase, amplitude and mesor.

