#### Secondary outcome measures

Analysis of the influence of sex on the CR by comparison of CR profiles of males and females. Investigation of the seasonality of CR by collection of saliva samples during two seasons (spring/summer and fall/winter). Analysis of the influence of age on the CR by comparison of CR profiles of younger probands (age between 13 and 18 years old) and profiles of older and younger adults, considering participants between 18–39 and 40–60 years old in separate groups.

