#### Analysis for primary endpoint

Amplitude, phase and mesor of the circadian data for the subgroups according to sex, age and season will be estimated per core clock gene using cosinor (harmonic) regression. The null hypothesis that there is no circadian rhythmicity (H_0_ = 0) is tested against the alternative hypothesis that a circadian rhythmicity pattern exists (H_A_≠0). The study is considered successful if rhythmicity is detected in some of the measured genes.

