#### Analysis for secondary endpoints

Differences in CR and mean gene expression level between subgroups, with respect to sex, age, seasons and physical performance, will be evaluated by CircaCompare [57] to estimate and observe differences between CR, specific to the characteristic desired (mesor, amplitude and phase). The methodology proposed by Parsons *et al*. [57] will be used for exploratory purposes, and circadian curves will be estimated per individual and sampling round. Additionally, correlations between molecular data and physical exercise measurements, as well as for hormonal data (melatonin and cortisol) and activity data (smart-tracker) will be calculated.

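### A Bonferroni divisor of ten does not hold the stated global 0.05, because it counts neither genes nor rhythm parameters

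*Protocol article*

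**What the plan says.** The Sample size estimation section names the family it protects as "comparisons between gender and age subgroups and various seasons". It then states: "in total up to 10 comparisons) the type I error is set to 0.005 according to the Bonferroni correction". The stated aim is "to hold the global significance level of α = 0.05". The ten comparisons are not listed, and neither genes nor rhythm parameters are mentioned in the count.

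Other sections describe what is tested:

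- Primary outcome measure: "Time series analysis of 8 core-clock and clock-controlled genes", with GAPDH named in addition as the reference gene.
- Secondary outcome measures: two sexes, three age groups and two seasons, for example "Analysis of the influence of sex on the CR by comparison of CR profiles of males and females".
- Analysis for primary endpoint: amplitude, phase and mesor "for the subgroups according to sex, age and season will be estimated per core clock gene". A rhythmicity hypothesis follows, and success is declared when some unspecified number of genes is rhythmic.
- Analysis for secondary endpoints: group differences by CircaCompare, "specific to the characteristic desired (mesor, amplitude and phase". The same section describes the use of that methodology as exploratory.
- Primary objective: the evaluation of sex, season and age effects is placed here, under the primary objective.

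**The concern.** Bonferroni holds a global level only if the divisor is at least the number of tests in the protected family. Here the divisor counts group contrasts, while the analysis sections repeat each contrast over several genes and possibly over three rhythm parameters. If the true count exceeds ten, the printed guarantee is false. A reader would then give a sex, age or season difference at p < 0.005 more protection than it has.

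The primary endpoint is exposed as well. Its success rule sets no minimum number of rhythmic genes, so a single false positive can count toward success. Under such a rule the error rate depends on how many gene-level tests are run.

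**Working it through.** **The plan's own figures.** 0.05 / 10 = 0.005, as stated. The rhythmicity test is described thus: "Rhythmicity will be tested using the F-test which compares the fitted model against a restricted model". Taking that F-test with 2 and n − 3 degrees of freedom and noncentrality n × r² / 2 (evenly spaced sampling), r = 0.82 and α = 0.005, power first reaches 0.80 at n = 52 (0.8002). This is the plan's number. The arithmetic is sound; the question is what ten counts.

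**Inputs.**
- Genes: 8 targets (Primary outcome measure). Four of them, BMAL1, PER2, CRY2 and NR1D2, belong to the core clock as the Introduction lists it.
- Subgroups: 2 sexes + 3 age groups + 2 seasons = 7 (Secondary outcome measures).
- Contrasts: 1 sex + 3 age pairs + 1 season = 5. The three age pairs are inferred from the three groups.
- Parameters: 3 (Analysis for secondary endpoints).

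**Formulas.** For m tests at 0.005, the Bonferroni bound is m × 0.005. With independent tests and all nulls true, the familywise error is 1 − 0.995^m.

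**Group differences**

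| Reading | m | Bound | If independent |
|---|---|---|---|
| 5 contrasts × 8 genes, one test each | 40 | 0.20 | 0.18 |
| 5 contrasts × 8 genes × 3 parameters | 120 | 0.60 | 0.45 |

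One gene with three parameters already gives 5 × 3 = 15 tests (bound 0.075). Restricting to the four core-clock genes with one test each gives 5 × 4 = 20 (bound 0.10). Counting only the two teenager-versus-adult age pairs gives 4 contrasts × 8 genes = 32 (bound 0.16). A divisor of ten covers at most two genes on one parameter (5 × 2 = 10). Over 120 tests the expected number of false positives under a complete null is 120 × 0.005 = 0.6.

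These counts omit the comparisons by physical performance and of mean expression level that the secondary analysis section also names.

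**Primary rhythm test**

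| Reading | m | Bound | If independent |
|---|---|---|---|
| 8 genes, pooled data | 8 | 0.04 | 0.04 |
| 4 core-clock genes × 7 subgroups | 28 | 0.14 | 0.13 |
| 8 genes × 7 subgroups | 56 | 0.28 | 0.24 |

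**Effect on sample size**, keeping the plan's r = 0.82 and its unit of n, so that only α changes:
- 8 pooled tests: 0.05 / 8 = 0.00625, n = 51, below the stated 52.
- 28 tests: 0.05 / 28 = 0.00179, n = 61.
- 56 tests: 0.05 / 56 = 0.00089, n = 67. Power at n = 52 falls to 0.61.

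**The case against.** Four objections deserve an answer.

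1. *The group differences are exploratory.* The secondary analysis section says so of the CircaCompare methodology, and its wording does not commit to testing all three parameters for every gene and contrast. So 120 is not an established confirmatory family. This stands, but it does not rescue the claim. The sample size section names these same group comparisons as what the correction protects, and the Primary objective section includes them. The two descriptions conflict, and one test per gene and contrast already gives 40.

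2. *The primary family may be small.* In Analysis for primary endpoint, the subgroups appear in the sentence on estimation, while the hypothesis test is stated separately without them. If rhythm is tested once per gene on pooled data, eight tests at 0.005 stay within 0.05. This reading is legitimate. The text does not choose it, so 0.28 cannot be given as the only answer either.

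3. *All genes may have to be rhythmic.* The sample size section states success without the word 'some', and a rule requiring every gene would need no correction across genes. The primary analysis section states the weaker rule, and the two must be reconciled.

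4. *An unseen analysis plan may list the ten comparisons.* It may. A list of ten would still not cover the tests this article describes.

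A reader might also infer that several chance differences are to be expected. The figures do not support that: 0.6 are expected over 120 tests. Nor should 8 genes, 7 subgroups and 3 parameters be multiplied to 168. The rhythm F-test is one test per gene and subgroup, and the parameters enter only in the group differences.

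**Conclusion.** The point holds. For the group comparisons it names, the plan's statement that 0.005 holds a global 0.05 is not true of the analyses described. The guaranteed bound is 0.20 on the modest count of 40 tests. It is 0.60 on 120 tests, and that figure depends on treating the CircaCompare tests as confirmatory. For the primary rhythm test the bound runs from 0.04 to 0.28 by reading, so the guarantee is undetermined there rather than shown to fail.

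The bounds need no assumption about dependence. The independence figures are illustrative only, because genes and overlapping subgroups are correlated and the true error rate is unknown. The defect is an incompletely defined family of tests, not an arithmetic slip.

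**What to change.** **Rhythm.** Define the confirmatory family as the eight pooled gene tests with Holm, and state how many rhythmic genes make the study a success, in the same words in both sections. The first Holm step is 0.05 / 8 = 0.00625, looser than 0.005, so the stated sample size need not rise on this account. Label rhythm fits within sex, age and season subgroups descriptive.

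**Group differences.** Choose one of two courses.
- Run one joint test of mesor, amplitude and phase per gene and factor: 8 genes × 3 factors = 24 tests. Use Holm (first step 0.05 / 24 = 0.0021) or false discovery rate control. Interpret single parameters and age pairs only where the joint test passes. If the false discovery rate is chosen, the text should say so and not claim a global 0.05.
- Label all group differences exploratory, in line with the secondary analysis section, and delete the statement that 0.005 holds a global 0.05 for them.

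Under the first course with Holm, say that 0.05 is held within each of the two families separately.

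**Cost.** The change is to analysis wording, with no new data collection. Some single-parameter or subgroup results will no longer be called significant. It should be settled before the data are analysed.

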In order to detect an intrinsic effect of r = 0.82 as significant at α = 0.005 and achieve a power of 0.8, a sample size of 52 is necessary (**Fig 2**). The sample size was estimated by R package CircaPower [40]. A dropout rate of 10–15% [41–44] is generally considered for calculating the sample size in clinical studies although there is no universal filter. As a compromise for potential higher dropout due to the longitudinal design of our study, we considered a dropout of 12% in our sample size estimation, and calculated a population of 59 participants to be sufficient to allow for the planned comparisons in the subset of a) females vs males or b) age groups or c) seasons. Participants will be distributed evenly for comparisons (e.g., for sample size) or appropriate statistical measures will be taken, by using statistical tests considering unequal sample size. Participants for whom there are no saliva samples collected are considered as dropout.

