**Fig 2 pone.0293226.g002:**
[figure not shown]
Graphical illustration of sample size estimation for the study protocol. The plot illustrates the identification of CR parameters based on *BMAL1* gene expression, which is then used to determine of sample size values and corresponding test power. Dashed red line indicates the optimal sample size (N) that needs to be collected for the detection of significant results according to pre-determined thresholds (α = 0.005; power = 0.8; r = 0.82). Accordingly, by considering a dropout rate of 12% a sample size of 59 participants was determined as needed to successfully assess the null hypothesis.

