### Data collection

#### Circadian rhythm monitoring from saliva samples

Saliva samples will be collected by the participants at home using home-kits. As a good practice for structuring circadian studies several parameters will be considered, such as sampling frequency, number of repetitive cycles or sources of biological specimen [47, 48]. For saliva collection a home kit from TimeTeller^®^ (TimeTeller GmbH, Hamburg, Germany) will be used, and sample collection carried out following the instructions of the provider, according to the previously established sampling protocol and RNA extraction and quantification [34]. During sampling, participants are advised to carry out their normal daily routine and collect a total of 8 saliva samples (with 4-hours sampling interval e.g., Day1: 9 a.m.; 1 p.m.; 5 p.m.; 9 p.m.; Day 2: 9 am; 1 p.m.; 5 pm; 9 pm) during each sampling round (**Fig 1B**). Participants are advised not to drink or eat 1 hour prior to their sampling time. The samples should be directly shipped to the lab for analysis using an enclosed package. Should this not be possible, the samples can be stored at room temperature, for a few hours or at 4°C for short-term (up to a week) or at -20°C (refrigerator) for long term storage, till shipment is possible. Further analysis including RNA quantification will be carried out by TimeTeller^®^, and the results provided in the form of individual circadian profiles.

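### The sample size of 52 for 80% power matches sampling spread evenly over 24 h; under the planned 12-hour window, 52 independent samples give 26% to 90% depending on when the gene peaks

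*Protocol article*

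**What the plan says.** The section on sample size estimation in the protocol article sets up a single sinusoid with independent, identically distributed normal errors, and defines n as the total count of samples. The inputs are:

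- Test: "Rhythmicity will be tested using the F-test which compares the fitted model against a restricted model".
- Significance level: "the type I error is set to 0.005 according to the Bonferroni correction".
- Effect size: "an amplitude (A) of 1.11 is estimated for" BMAL1, "the standard deviation of residuals (s) is 1.36", and hence "an estimate of the intrinsic effect height of r = A/s = 0.82".
- Result: to "achieve a power of 0.8, a sample size of 52 is necessary", obtained with the CircaPower package.

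The caption of Fig 2 repeats this: "Dashed red line indicates the optimal sample size (N) that needs to be collected for the detection of significant results". Neither place gives the sampling times or the phase that entered the calculation. The section then treats 52 as participants and raises it to 59 for 12% dropout.

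The schedule is in the section on circadian rhythm monitoring from saliva: 8 samples per round, "with 4-hours sampling interval e.g., Day1: 9 a.m.; 1 p.m.; 5 p.m.; 9 p.m", with the same four clock times on day 2. The study design section plans four such rounds per participant.

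**The concern.** The power of a cosinor F-test depends on how the sampling times cover the cycle. With even coverage, power is the same at every phase. With coverage of half the cycle it is not: a gene whose peak or trough falls mid-window shows less variation across the sampled times than one whose peak and trough fall at the ends of the window.

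If the calculation assumed even coverage, the stated 80% does not describe the planned schedule at most phases. Genes, or sex and age groups, with equal true amplitude but different phase would also differ in precision and in the chance of being called rhythmic. This bears on the primary analysis, which tests rhythmicity gene by gene, and on the secondary comparisons of mesor, amplitude and phase. The article's introduction itself expects phase to differ by sex and age.

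**Working it through.** **Inputs.** r = 0.82 (1.11/1.36 = 0.816, rounded), alpha = 0.005 and n = 52 from the sample size section; times 9, 13, 17 and 21 h from the saliva monitoring section; period 24 h.

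**Formula.** The F statistic has 2 and n − 3 degrees of freedom and noncentrality λ = n · r² · d. Here d is the variance of cos(2π(t − peak)/24) over the sampling times t. Power is the upper tail of the noncentral F beyond the 0.005 critical value, which is 5.91 for 2 and 49 degrees of freedom.

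**Step 1: the protocol's own figure.** Even coverage gives d = 0.5 at every phase, so λ = 52 × 0.6724 × 0.5 = 17.48. Power is 0.8002 at n = 52 and 0.788 at n = 51, so 52 is the smallest n that reaches 80%. With r unrounded, power at 52 is 0.795 and 53 would be needed, a trivial difference.

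**Step 2: the planned times.** Repeating the same four times on day 2 leaves d unchanged. For these times d = 0.406 + 0.219 · cos(4π(peak − 9)/24).

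| Peak time (h) | d | λ at n = 52 | Power at n = 52 | n for 80% |
|---|---|---|---|---|
| 9 or 21 | 0.625 | 21.85 | 90.3% | 43 |
| 0, 6, 12 or 18 | 0.406 | 14.20 | 67.8% | 63 |
| 3 or 15 | 0.1875 | 6.56 | 25.8% | 130 |

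Simulation with 40,000 runs per phase agrees: 25.6% and 26.1% at 3 and 15 h, and 90.1% and 90.2% at 9 and 21 h. Averaged over phases, power is 62.7%. It equals 80% where d = 0.5, at peaks near 6.9, 11.1, 18.9 and 23.1 h. It is higher from 6.9 to 11.1 h and from 18.9 to 23.1 h, and lower at the remaining phases, about 64% of the cycle.

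**Step 3: the sample counts that the design yields.** These use the same formula and still assume independent errors.

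| Unit analysed | Samples | Worst phase | Best phase |
|---|---|---|---|
| One participant, one round | 8 | 1% | 3% |
| One participant, four rounds | 32 | 11% | 59% |
| 26 participants, one round | 26 × 8 = 208 | 97.3% | over 99.99% |
| 52 participants, one round | 52 × 8 = 416 | over 99.99% | over 99.99% |

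**Step 4: precision, which does not depend on n.**
- For a 15 h peak, the cosine at the four times is 0, 0.866, 0.866, 0. Its mean is 0.433 and its mean square is 0.375, so d = 0.375 − 0.1875 = 0.1875.
- The correlation between the mesor and amplitude estimates is −0.433/√0.375 = −0.71.
- For a 9 h peak, the cosine is 1, 0.5, −0.5, −1. Its mean is 0, so there is no such correlation, and d = 0.625.
- The ratio of amplitude standard errors, 15 h to 9 h, is √(0.625/0.1875) = 1.83.

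The ratio and the correlation stay the same however many participants are added on this schedule.

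**The case against.** **A reader might infer that the study's true power is 26% to 90%.** The documents do not support that. The range belongs to 52 single independent samples, and no planned analysis has that number. Under the stated independence model, the 416 samples that 52 participants give in one round have power above 99.99% at every phase. The 130 samples needed at the worst phase come from about 16 participants in one round (130/8 = 16.25). Nor does 99.99% describe the study: samples from one person are unlikely to be independent and people differ in phase, and the article quantifies neither. Real pooled power cannot be derived from it.

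**A reader might also infer that 52 can arise only from even coverage.** That is too strong. The daytime schedule also gives 80% at n = 52 if the peak lies near 6.9, 11.1, 18.9 or 23.1 h. The BMAL1 phase comes from a previous study and is not stated, and Fig 2 could not be viewed. Even coverage is the likely input, not a proven one. If BMAL1 peaks between 6.9 and 11.1 h or between 18.9 and 23.1 h, 52 is sufficient for that gene under the model.

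**Three further points have weight.**
- The range over phase holds r at the BMAL1 value; the article gives no r for the other genes.
- Success requires rhythmicity in only some genes, so one unfavourable phase does not fail the study.
- The clock times are an example. A common shift of the start changes which phases are favoured, not the range. Staggered starts would help somewhat: if starts were spread equally over 7, 8, 9, 10 and 11 a.m. (an assumption), d at the worst phase would be 0.244 and power at n = 52 would be 37%.

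These points limit the claim about pooled detection. They do not show that the stated 80% follows from the planned schedule, and they leave the precision result in place. They also carry less weight for the curves planned per individual and sampling round, where sample counts are small.

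**Conclusion.** The point holds as a mismatch between the sample size calculation and the sampling plan. The arithmetic of 52 is sound for even 24-hour coverage, but the planned window covers about 12 of 24 hours, and neither sampling times nor phase is stated. At the protocol's own n, r and alpha, power on the planned times runs from 26% to 90% with phase and is below 80% for about 64% of possible phases.

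The section also counts n in samples and then applies it to participants. The 80% is therefore not the power of the pooled analysis or of a per-individual fit. The loss of precision at unfavourable phases (amplitude standard error 1.83 times as large, correlation of −0.71 with mesor at 15 h) holds at any n.

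The results rest on the example times being typical, a 24-hour period, independent errors, and r = 0.82 at every phase. This should be corrected, but it is not a reason to change the conduct of the study.

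**What to change.** - Rerun the calculation with the planned sampling times and the BMAL1 peak time from the previous study.
- State whether n counts samples or participants. If participants, allow for repeated samples within a person.
- Restate n or power in the sample size section and in Fig 2, with its range over phase for genes whose peak time is not known.
- State that failure to detect rhythm at an unfavourable phase (near 3 or 15 h for the example times) is inconclusive, above all in fits per individual or per round.
- Report amplitude with its confidence interval beside mesor.

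This takes a few lines of code and a revised figure, and changes nothing for participants, kits or sampling. The downside is that the stated power may become less favourable at some phases.

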### Study design

This is a prospective, monocentric, non-interventional observational study, which uses data collected from healthy and physically active participants in Germany **(Fig 1)**. Saliva samples will be collected by the participants themselves at home. For the analysis of potential seasonal variations, samples are grouped into a spring/summer batch and autumn/winter batch. Two rounds of saliva collection will take place between April-September 2022/2023 as spring/summer batch; and two rounds in October-March 2022/2023 (based on DST/standard time change date), as autumn/winter batch. In total four sampling rounds per person, till the end of 2023, are aimed to be collected. For each sampling round, 8 saliva samples per sampling kit, at four time points per day, should be collected during two consecutive days **(Fig 1)**.

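### The sample size of 52 is a count of independent saliva samples for a rhythm test; restated as 59 participants, it shows no power for the sex, age and season comparisons it is said to cover

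*Protocol article*

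**What the plan says.** Under Sample size estimation, the protocol article sets up a single sinusoid for BMAL1 expression, "whereby n is the total number of samples", with errors "identically and independently distributed from" a normal distribution. The hypothesis is stated as follows: "The null hypothesis that there is no circadian rhythmicity" is set against the alternative that a rhythm exists. On the test it says: "Rhythmicity will be tested using the F-test which compares the fitted model against a restricted model". For multiplicity, "the type I error is set to 0.005 according to the Bonferroni correction", covering the sex, age and season comparisons, "in total up to 10 comparisons". With A = 1.11 and s = 1.36, so r = 0.82, the required size for 80% power is given as 52.

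The next paragraph applies 12% dropout, defined at participant level, and reports that it "calculated a population of 59 participants to be sufficient to allow for the planned comparisons in the subset of a) females vs males", age groups or seasons. The Fig 2 legend says instead that the 59 participants are needed to assess the null hypothesis, which is the rhythm hypothesis.

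Under Study design, each round yields "8 saliva samples per sampling kit, at four time points per day" over two days, and four rounds are planned, so a complete participant gives 32 samples. Under Analysis for secondary endpoints, the subgroup differences are evaluated with CircaCompare on mesor, amplitude and phase.

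**The concern.** Two things change between the calculation and the conclusion drawn from it. The unit moves from samples to participants, one for one, although each participant contributes up to 32 samples. The hypothesis moves from whether a rhythm exists to whether rhythms differ between groups. Neither step has a calculation behind it.

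The sex, age and season comparisons are in the stated aim and in the primary objective as well as among the secondary outcomes. A reader who takes the sufficiency statement at face value could read a null sex, age or season result as coming from a comparison with 80% power, when no such power was worked out.

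**Working it through.** **1. Reproduce the plan's figure.** Inputs from Sample size estimation: r = 0.82, alpha = 0.005 (0.05/10), power 0.80. For a cosinor F-test with evenly spread sampling times, the statistic is noncentral F with 2 and n − 3 degrees of freedom and noncentrality n·r²/2.

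- n = 51: power 0.788
- n = 52: power 0.800

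So 52 is the number of independent observations for one rhythm test. The formula contains no group term, no difference to detect and no person-level variance.

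**2. Follow the unit.** 52/0.88 = 59.1, reported as 59. The sample count was therefore carried over as a participant count. Read as samples, 52 corresponds to 52/8 = 6.5 participants at one round, or 52/32 = 1.6 participants at four rounds.

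**3. Rhythm detection within subgroups, with the planned sampling.** Assume 52 evaluable participants split evenly, and keep the plan's independence assumption. One round gives 26 × 8 = 208 samples per sex and about 17 × 8 = 136 per age group (three groups). Power at alpha 0.005 exceeds 0.999 in both. Rhythm detection is not where the difficulty lies.

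**4. What a comparison would need.** Take an amplitude difference between the sexes, with 26 participants per sex, m samples per person and s = 1.36. Let τ be the between-person SD of amplitude, which the article does not give and which is assumed here. With evenly spread times, the sampling variance of one person's amplitude is approximately 2s²/m, so

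SE = √[2(τ² + 2s²/m)/26].

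The difference detectable with 80% power at two-sided alpha 0.005 is (2.807 + 0.842) × SE = 3.649 × SE. Here 2s² = 3.699, so 2s²/m is 0.1156 for m = 32 and 0.4624 for m = 8.

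| τ (assumed) | m = 32 | m = 8 |
|---|---|---|
| 0 (all samples independent) | 0.34 | 0.69 |
| 0.2 | 0.40 | 0.72 |
| 0.6 | 0.70 | 0.92 |
| 1.0 | 1.07 | 1.22 |

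For example, τ = 0.2 and m = 32 give SE = √[2(0.04 + 0.1156)/26] = 0.109, and 3.649 × 0.109 = 0.40. Against the mean amplitude of 1.11, the table runs from 31% (0.34/1.11) to 110% (1.22/1.11).

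**5. Limits of the illustration.** It uses a normal approximation and evenly spread times, whereas the example schedule (9 a.m. to 9 p.m.) leaves the night unsampled. It covers amplitude and a between-person contrast only. Season is a within-person contrast, with two rounds planned per batch for each participant. The table does not represent it, and the plan gives no calculation for it.

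**The case against.** The strongest defence is that the success criterion is rhythmicity, that this is the hypothesis powered, and that the Fig 2 legend ties the 59 participants to it. Counting people as samples makes the study larger than the formula requires for that test. The sex, age and season differences are listed as secondary outcomes and analysed as secondary endpoints, and alpha was already divided for them. Most of this stands: the rhythm test is amply sized. But a Bonferroni alpha limits false positives and does not supply power for a difference. The text also goes beyond the legend by asserting sufficiency for the comparisons.

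A reader might infer something stronger, namely that the comparisons are badly underpowered. Splitting 52 observations in half gives 33% power for rhythm within one sex (n = 26), and splitting them in three gives 14% within an age group (n = 17). For 26 against 26 observations the SE of an amplitude difference is 1.36 × √(4/26) = 0.53 and the detectable difference 1.95. The documents do not support that reading. These figures assume one saliva sample per participant, and the plan has 8 per round over up to four rounds. With 32 samples per person, an SE of 0.53 would require τ = √(13 × 0.5334² − 0.1156) ≈ 1.9, or about 170% of the mean amplitude.

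Another possible defence is that a journal article condenses a fuller plan. That would excuse silence on the comparisons. It does not excuse a positive statement that the calculation shown does not bear out.

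**Conclusion.** The point holds as an unsupported inference. It is not an arithmetic error: 52 is reproduced and 59 is within rounding. The 80% power applies to detecting a BMAL1 rhythm in 52 independent samples. For sex, age and season differences in mesor, amplitude and phase, power is not shown. Nor is it shown to be inadequate: for sex, the detectable amplitude difference ranges from 0.34 to 1.22 depending on samples per person and on an assumed between-person SD of 0 to 1.0. That range, roughly a third of the mean amplitude to slightly more than all of it, is too wide to support a claim of sufficiency either way. It rests on 26 participants per sex, alpha 0.005 and s = 1.36.

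Severity is should-fix. The study is observational, its declared success criterion is the hypothesis that was powered, and the correction changes neither recruitment nor analysis.

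**What to change.** Keep the 59 participants. In Sample size estimation and in the Fig 2 legend, state that 52 is the number of independent samples needed for the rhythm test at alpha 0.005, and delete the claim that 59 participants suffice for the planned comparisons.

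In its place, do one of two things:

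- Report minimum detectable differences in mesor, amplitude and phase, treating sex and age as between-person contrasts and season as a within-person contrast. Cover a stated range of variance components and 8 to 32 samples per participant. The range of samples matters because only participants with no saliva samples count as dropouts, and rounds affected by infection are discarded, so an evaluable participant may have far fewer than 32.
- Label these comparisons as not formally powered.

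The first option costs a short simulation and, if available, variance estimates from the previous study; the second costs a sentence. In both cases the stated property becomes less favourable than the present text.
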